### Recruitment

Participants for the study will be recruited through diverse channels, encompassing in-hospital and subway advertisements, as well as the outpatient department of the hospital. This multifaceted recruitment strategy aims to reach a broad and representative pool of potential participants for the clinical trial.

### Assignment of interventions

The randomization process will be conducted by a statistician who is not involved in the execution or evaluation of the clinical trial. Utilizing SAS^®^ Version 9.4 (SAS Institute, Inc., Cary, NC), the statistician will employ a block randomization method to randomly assign each subject to either the experimental or control group, ensuring a 1:1 chance of selection. Following the creation of the randomization list, the statistician will seal and securely store the randomization table. Sealed envelopes will be prepared in such a way that the seal can be checked, and they will be managed separately by the research director. The test staff who provide the intervention to the patients will allocate the subjects by opening randomization envelopes in the predetermined order in front of the subjects. The opened envelopes will be stored separately, with the date of opening and the signature of the test staff written on them.

Before beginning the clinical trial, the investigator will explain the ICF to the participants and obtain written consent for the clinical trial from them based on their free will after ensuring that they understand what is expected of them. The subjects will be given a screening code once they have given their consent. Subjects who agree to take part in this clinical trial will be assigned a screening number in the manner described below.

# DJ-S-### [DJ: Daejeon Korean Medicine Hospital of Daejeon University, S: Screening, ###: Serial number (001, 002, 003, …)] (e.g., DJ-S-001: Daejeon Korean Medicine Hospital of Daejeon University’s 1st applicant for screening).

Only eligible subjects who meet the inclusion and exclusion criteria through eligibility assessment will be assigned an identification code in the manner described below.

# DJ-E-### [DJ: Daejeon University Daejeon Oriental Medicine Hospital, E: Enrollment, ###: Serial number (001, 002, 003,…)] (e.g., DJ-E-088: Daejeon Korean Medicine Hospital of Daejeon University’s 88th enrolled subject).

### Blinding

The test staff (i.e., investigator) will be divided into intervention staff and evaluation staff. The intervention staff will perform MARS-PD intervention, provide medical consultations to test subjects, and record case report forms (CRFs). Due to the nature of the intervention method used in this clinical trial, blinding of the subjects and the intervention staff will not be possible. Only blinding of the evaluation staff and statisticians will be possible in this study. To reduce the risk of unblinding caused by electronic medical records (EMRs) and CRFs, and orders will be recorded under the name of the intervention staff, not the evaluation staff. The evaluation staff will determine the research subjects’ eligibility, obtain signed ICF from the subjects, assign screening numbers and identification codes to the subjects, and perform evaluations. The evaluation staff should not be aware of the subjects’ treatment. The clinical research coordinator (CRC) will manage the subjects’ schedules and complete the CRFs as part of the basic clinical trial work. Blinding of the CRC cannot be maintained. The outcome assessor will be blinded.

### Data collection and management

The data will be collected and recorded by the intervention staff using CRF. The data will be stored confidentially in line with the National Institute for Korean Medicine Development’s (NIKOM) personal information protection policy. A copy of all documents related to this trial, including signed ICFs, CRFs, and other participant records, will be kept in document storage room for three years.

### Statistical analysis

To calculate compliance for each subject, we will use the following formula:

$$Compliance\left(\%\right)=\frac{number\;of\;interventions\;actually\;conducted}{number\;of\;interventions\;originally\;planned}$$

Throughout the trial, it is imperative that compliance (%) remains at or above 75%. Subjects falling below this threshold will be considered insufficiently compliant and subsequently excluded from the per-protocol (PP) analysis. The efficacy analysis will be primarily assessed based on the full analysis set (FAS) principle, followed by the PP principle for primary and secondary outcomes.

The FAS analysis will be carried out on cases that meet the principle of intention-to-treat (ITT). The FAS analysis will exclude cases falling into the following categories: (1) subjects not meeting the main eligibility criteria, (2) those not receiving the intervention specified in the protocol, and (3) individuals who were never evaluated after randomization with no collectable data.

On the other hand, the PP analysis will be carried out on cases that have successfully completed the entire trial process without any protocol violations. The PP analysis will exclude cases meeting any of the following criteria: (1) subjects dropping out during the intervention period, (2) violation of eligibility criteria, (3) compliance falling below 75%, and (4) any other serious violations of the clinical trial protocol.

By adopting this approach, we aim to evaluate the results conservatively, considering PD’s natural tendency to worsen over time. Statistical analysis will be conducted using the two-tailed test method, and a p-value of < .05 will be deemed statistically significant. In the event of missing values, appropriate imputation methods will be employed based on the underlying cause.

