### Interventions

At a 1:1 ratio, patients will be assigned to either the experimental (MARS-PD intervention) or control (usual care with no additional intervention) groups. Those in the experimental group will undergo the MARS-PD intervention twice a week for 8 a span of weeks, totaling 16 visits. The intervention will be administered by Doctors of Korean Medicine with a minimum of one year of clinical experience in the relevant field, as detailed in the authors’ previous work [16]. In contrast, patients in the control group will adhere to their usual care without any supplementary interventions. Given that the number of steps per day constitutes one of our secondary outcomes, all willing participants, regardless of their group assignment, will receive Samsung Galaxy Fit2 smart band (Samsung Electronics Co., Ltd., Suwon, South Korea), and application-based lifestyle guidance.

During the test period, participants are allowed to engage in personal exercise. However, doctor-prescribed manual therapy, exercise therapy, and rehabilitation treatment specifically tailored for PD are not permitted. This restriction aims to maintain consistency in the intervention conditions and isolate the effects of the MARS-PD being evaluated in the trial.

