### Standards for concomitant drug

The utilization of antiparkinsonian drugs, such as levodopa (L-dopa), Catechol-O-methyltransferase (COMT)) inhibitor, Dopamine agonist, Monoamine oxidase B (MAO-B) inhibitor, etc., will be permitted if the dosage has remained stable for more than 4 weeks preceding the initiation of participation in the clinical trial. The prescribed drug dosage must be maintained throughout the trial period. Additionally, medications employed for the temporary treatment of conditions other than PD may be allowed after consultation with the investigator. All concomitant medications, irrespective of their purpose, should be documented with detailed drug information, including product name, dose, purpose and duration of administration, etc., in the case report forms (CRF). While there are no drugs that are pre-determined to be prohibited, the investigator retains the discretion to restrict the use of medications that may potentially influence the trial outcome, such as corticosteroids, female hormones, etc. This approach ensures thorough documentation and monitoring of medication usage throughout the study.

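### The 75% compliance exclusion can act only in the MARS-PD arm, so the per-protocol comparison is selected on one side and cannot be relied on as conservative

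*Protocol article*

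**What the plan says.** All references are to the protocol article.

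- **Compliance (Statistical analysis).** The measure is meant for everyone: "To calculate compliance for each subject, we will use the following formula", namely interventions conducted divided by interventions planned. The threshold is firm: "Throughout the trial, it is imperative that compliance (%) remains at or above 75" percent. The consequence is stated: "Subjects falling below this threshold will be considered insufficiently compliant and subsequently excluded from the per-protocol (PP) analysis".
- **Planned sessions (Interventions).** The experimental arm is treated twice weekly for 8 weeks, "totaling 16 visits". By contrast, "patients in the control group will adhere to their usual care without any supplementary interventions".
- **All PP exclusions (Statistical analysis).** The four grounds are "1) subjects dropping out during the intervention period, (2) violation of eligibility criteria, (3) compliance falling below 75%, and (4) any other serious violations". None is expressly limited to one arm.
- **Role of the sets (Statistical analysis).** FAS is the primary basis for efficacy and PP follows, for both primary and secondary outcomes. After describing both sets the section says: "By adopting this approach, we aim to evaluate the results conservatively", with reference to the progressive course of the disease.
- **Baseline-adjusted analyses (Efficacy evaluation).** Secondary outcomes are to be analysed by ANCOVA or multiple regression with baseline variables. The primary outcome moves from a t-test to ANCOVA if the groups differ at baseline. Where the baseline variable is a covariate, the section calls for a PP analysis with no handling of missing values.

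**The concern.** Attendance is observed after randomisation and may be related to how the patient is doing. A MARS-PD patient who stays in the trial but misses sessions because the exercise is tiring or seems not to help leaves the PP set. A control with the same course has no sessions to miss and stays in. The two PP groups are then no longer comparable by randomisation.

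The Sample size section tests equality of mean change against a two-sided difference. In that setting, selecting adherers in the treated arm alone can create or enlarge an apparent benefit. A PP result in favour of MARS-PD could then be read as cautious confirmation of the FAS result, or, where PP is the set for a baseline-adjusted analysis, as the result itself. Correcting the FAS definition would not remove this problem.

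**Working it through.** **1. The plan's own figure.** Inputs from Sample size: difference 5, SD 6.5, two-sided alpha 0.05, power 90%. Then 2 × (1.96 + 1.28)² × 6.5² / 5² = 35.48, which rounds up to 36 per group as stated. The plan enrols 44 per group. SD 6.5 is carried forward below.

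**2. Whom the rule can remove.**
- MARS-PD: 0.75 × 16 = 12 sessions. Twelve sessions give 12/16 = 75% (kept); eleven give 11/16 = 68.75% (removed).
- Control: 0 conducted over 0 planned is undefined, so no control can fall below 75%.

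**3. Size of a one-sided selection.** Assume no true effect. Let q be the share of the MARS-PD arm removed for low compliance and r the correlation between adherence and improvement. The documents give neither, so both are varied. If the lowest-adherence fraction q is cut from a normal distribution, then

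spurious shift = r × 6.5 × φ(z_q) / (1 − q).

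The factor φ(z_q)/(1 − q) is:
- q = 5%: 0.1031/0.95 = 0.109
- q = 10%: 0.1755/0.90 = 0.195
- q = 20%: 0.2800/0.80 = 0.350
- q = 30%: 0.3477/0.70 = 0.497

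For example, q = 20% and r = 0.5 gives 0.5 × 6.5 × 0.350 = 1.14 points.

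**4. Type I error.** Two-sided 5% t-test by the noncentral t distribution, with 44 × (1 − q) MARS-PD patients (rounded down) and 36 to 44 controls. The small loss of variance from the cut is ignored.

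| q | r | Shift toward MARS-PD (points) | Type I error |
|---|---|---|---|
| any | 0 | 0 | 5% |
| 5% | 0.2 | 0.14 | 5.1% |
| 10% | 0.3 | 0.38 | 5.7-5.8% |
| 10% | 0.5 | 0.63 | 7.0-7.2% |
| 20% | 0.3 | 0.68 | 7.2-7.4% |
| 20% | 0.5 | 1.14 | 11.2-11.9% |
| 30% | 0.5 | 1.61 | 16.8-17.9% |

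Starting instead from 36 per arm, with a normal approximation, q = 20% and r = 0.5 gives 10.8%. A negative r gives the same sizes in the opposite direction.

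**5. Scale.** The Sample size section cites a minimal clinically important difference of 2.3 to 2.7 points for MDS-UPDRS Part III and designs for 5. The largest shift shown, 1.61, is 60% to 70% of the former (1.61/2.7 and 1.61/2.3) and 32% of the latter.

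**The case against.** The strongest reply is that FAS is primary, that an adherence threshold in a secondary PP set is ordinary practice, and that a condensed article may leave its application to controls to the full protocol. The first part stands and limits the consequence for the primary conclusion. The last does not dispose of the point, because the rule is stated in full and, as stated, can act in one arm only.

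Three stronger readings are tempting, and the documents do not support them.

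- **That PP sets selected adherers against an unselected control arm.** Controls also leave PP for dropout, eligibility violations and other serious violations. For instance, "The prescribed drug dosage must be maintained throughout the trial period", so a control who worsens and has a dose change might be removed, which would work against MARS-PD. Likewise, MARS-PD patients who stop altogether during the 8 weeks are largely dropouts, a ground that covers both arms. The one-sided part is those who remain in the trial with 11 or fewer sessions.
- **That PP necessarily favours MARS-PD.** This needs a positive correlation between attendance and improvement, which the documents do not give. At zero there is no bias from this source, and if patients who do well skip visits it reverses.
- **That the article calls PP itself conservative.** The sentence follows the description of both sets and refers to the approach as a whole, with FAS first. The fair criticism is that the claim is not warranted for the PP part.

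It is also fair to say that the upper end of the range rests on q = 30% with r = 0.5. The plan's only attrition figure is 20% dropout overall, which is not a low-compliance rate.

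**Conclusion.** The point holds in a limited form. The compliance criterion can remove only MARS-PD patients, so PP applies a one-sided post-randomisation selection and has no claim to be conservative in a test for a difference. This part follows from the text and needs no assumption.

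Its size does need assumptions: 0 to 1.6 points and a type I error of 5% to about 18% over q = 5-30% and r = 0 to 0.5, with SD 6.5 and no true effect. Most combinations in the table lie well below the upper end, and the sign is not assured.

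The FAS-first order partly protects the primary conclusion. The protection is weaker for the secondary outcomes, and for the primary outcome if ANCOVA is triggered, because the Efficacy evaluation section appears to make PP the set when baseline is a covariate. The plan should be changed, but the point does not by itself invalidate the primary analysis.

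**What to change.** 1. State that the 75% criterion applies to the MARS-PD arm only, and that PP is supportive and cannot by itself support an efficacy conclusion.
2. Withdraw the statement about conservative evaluation as far as it covers PP.
3. In Efficacy evaluation, do not use PP as the set for baseline-adjusted analyses; run them on the same primary set as the other efficacy analyses.
4. If an effect in adherers is wanted, add a complier-average analysis of all randomised patients, with randomisation as the instrument and at least 12 of 16 sessions as the exposure.

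**Cost.** Changes of wording and one additional model on data already to be collected. The complier estimate has a wider interval than PP. It also assumes no effect below 12 sessions. With no control access during the trial it is roughly the all-randomised difference divided by the share reaching 12 sessions (with 80% reaching it, multiplied by 1/0.8 = 1.25), so it overstates the effect if fewer sessions have any benefit. It should therefore be labelled supplementary.

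### The primary full analysis set is called intention-to-treat but drops patients who do not receive the intervention, in practice MARS-PD non-starters who already know their arm

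*Protocol article*

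**What the plan says.** The Statistical analysis section sets the order of populations: "The efficacy analysis will be primarily assessed based on the full analysis set (FAS) principle", followed by per-protocol (PP). It describes the FAS in these terms: "The FAS analysis will be carried out on cases that meet the principle of intention-to-treat (ITT"). It then lists three FAS exclusions. The first is failure to meet the main eligibility criteria. The second is "2) those not receiving the intervention specified in the protocol". The third is "3) individuals who were never evaluated after randomization with no collectable data". The PP set has its own list: dropout during the intervention period, eligibility violation, compliance below 75%, and other serious violations. On the compliance rule it says: "Subjects falling below this threshold will be considered insufficiently compliant and subsequently excluded from the per-protocol (PP) analysis". The section adds that the approach is meant to be conservative, because Parkinson's disease tends to worsen.

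The Interventions section says what each arm gets. For MARS-PD: "Those in the experimental group will undergo the MARS-PD intervention twice a week", for 16 visits in all. For controls: "patients in the control group will adhere to their usual care without any supplementary interventions".

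Under Assignment of interventions, the staff who deliver the intervention "will allocate the subjects by opening randomization envelopes in the predetermined order in front of the subjects". The Blinding section confirms that neither patients nor intervention staff can be blinded.

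**The concern.** Intention-to-treat keeps patients in the arm to which they were randomised, whatever they go on to receive. An exclusion for not receiving the intervention contradicts that label. Two features of this trial make the conflict more than a matter of naming.

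- **The rule acts on one arm.** MARS-PD patients can fail to attend. Controls have no session or procedure to fail to attend.
- **The arm is known first.** A patient who learns of 16 extra visits may decline them, and the reasons may be related to outcome, for example frailty or low motivation.

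The MARS-PD arm could then be a selected group compared with an unselected control arm, in the analysis on which the efficacy conclusion rests. The article describes no all-randomised analysis that would reveal this. The Economic evaluation section also uses the FAS, so cost per QALY inherits the same population.

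**Working it through.** **1. The plan's own figures.** Inputs from the Sample size section: difference 5, SD 6.5, two-sided alpha 0.05, power 90%, dropout 20%, 44 per arm.

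n per group = 2 × (1.96 + 1.28)² × 6.5² / 5² = 35.5, so 36. This reproduces the stated 36. The stated 44 per arm agrees with 36 × 1.2 = 43.2, rounded up (36/0.8 would give 45). The point below does not depend on that difference.

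**2. Who can be removed.** Setting the sections side by side:

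| Step | MARS-PD | Control |
|---|---|---|
| Learns arm at envelope opening | yes | yes |
| Trial sessions planned | 16 | 0 |
| Can fail to receive the trial intervention | yes | nothing to receive |
| Removed from FAS by exclusion (2) | if never started | no route given |

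The same holds for the 75% criterion in PP. Compliance is sessions conducted divided by sessions planned, and controls have none planned, so that criterion can act only on MARS-PD.

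**3. Illustrative shift.** Let k of the 44 MARS-PD patients be removed, with a mean change d points worse than that of those kept. The mean of those kept then differs from the mean of all 44 by k × d / 44. Both k and d are assumptions. The document gives no never-start rate, and its 20% is an overall dropout figure.

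- k = 2, d = 3: 2 × 3 / 44 = 0.14 points
- k = 4, d = 5: 4 × 5 / 44 = 0.45 points
- d = 0: no shift
- d negative: the shift runs against MARS-PD

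Relative to the planned 5 points this is 0.14/5 to 0.45/5, about 3% to 9%.

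**4. Illustrative type I error.** Assume no true effect, SE = 6.5 × √(1/44 + 1/(44 − k)), a normal approximation, and gaps of 0.5 SD (3.25) or 1 SD (6.5).

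| k | d | Shift | Two-sided error |
|---|---|---|---|
| 4 | 3.25 | 0.30 | 5.5% |
| 4 | 6.5 | 0.59 | 7.0% |
| 8 | 3.25 | 0.59 | 6.9% |
| 8 | 6.5 | 1.18 | 12.8% |

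**5. Price of keeping everyone.** Suppose k non-starters get no benefit, the effect in starters is 5, and all 88 patients have data. The all-randomised effect is 5 × (44 − k)/44.

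| k | Effect | Power |
|---|---|---|
| 2 | 4.77 | 93% |
| 4 | 4.55 | 91% |
| 6 | 4.32 | 88% |
| 8 | 4.09 | 84% |

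**The case against.** **Dropping never-starters is a common modified intention-to-treat device.** True, and it is easiest to defend when knowledge of the arm cannot influence starting. Here it can, and the set is labelled intention-to-treat rather than modified.

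**Usual care might count as the specified intervention**, since the Interventions section covers both arms. The one-sidedness is indeed inferred from the definition of the control arm and is not stated. But the article names nothing that a control could fail to receive, so the practical effect stands.

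**The effect may be small.** This also stands. Both the share of non-starters and their outcome gap are assumed, and with 4 of 44 removed at a 3.25-point gap the type I error moves only from 5.0% to 5.5%.

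Three stronger readings are tempting, and the document does not support them.

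- *Patients who start and then stop also leave the FAS.* On its natural reading exclusion (2) covers non-receipt. Dropout and compliance below 75% are listed for PP only.
- *Both populations are known to favour MARS-PD.* That direction is plausible, but the document cannot establish it.
- *Only MARS-PD patients can leave the PP set.* This is true of the compliance criterion alone. Dropout, eligibility violation and other serious violations can remove controls too. PP already ranks after the FAS, and how compliance is scored for controls may be settled in the full protocol.

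**Conclusion.** The point holds for exclusion (2). The primary FAS, as written, is not intention-to-treat. In practice the exclusion removes MARS-PD patients who never start, after they know their allocation, and so it cannot be called conservative. This conclusion rests on the stated text and the definition of the control arm, not on any assumed number.

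The size and direction of the bias are unknown. The 0.14 to 0.45 points towards MARS-PD is an illustration that assumes 2 to 4 non-starters whose change would be 3 to 5 points worse. The shift is zero if they do not differ and reverses if they would have done better.

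**What to change.** - Delete exclusion (2) from the FAS. Analyse all randomised patients in their assigned arm, whatever number of sessions they received.
- Limit exclusion (1) to eligibility failures that predate randomisation and are judged blind to arm. This would be the only permitted removal, and the text should say so.
- Seek week-8 assessments for non-starters. Handle missing scores, including those of patients now under exclusion (3), by the plan's imputation, with a sensitivity analysis.
- Keep the non-receipt exclusion for PP or for a sensitivity analysis labelled modified intention-to-treat.
- Drop the claim of conservatism for this exclusion, and note that the 75% session criterion in PP can act only on the MARS-PD arm.

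**Cost.** This is more than wording, because non-starters must be followed to week 8. The estimate may be diluted: 4 of 44 non-starters without benefit turn a 5-point effect into about 4.55, with power of about 91% if all 88 have data. With 8 non-starters power is about 84%, below the planned 90%.
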